#### Oxygen saturation in the blood (SpO2)

Oxygen saturation in blood will be measured with a finger pulse oximeter at the time of PSG before and after one month and 3 months of intervention. Mean oxygen saturation, oxygen desaturation index (ODI), and proportion of time with SpO2 < 90%, will be evaluated.

#### Percentage of rapid eye movement (REM)

REM-AHI will be evaluated by calculating the number of events of AHI in REM sleep and dividing it by the amount of REM time with the help of PSG before and after one and three months of intervention

#### Electroencephalogram (EEG)

The pattern of EEG will be evaluated from PSG in the central lead C3-A2 at the apex of the cranium at 100 Hz sampling frequency to record Cortical arousals. Readings will be recorded before and after one month and three months of intervention for the participants of both study groups.

#### Electrocardiogram (ECG)

ECG patterns will be evaluated before and after one and three months of intervention. The ECG will be evaluated to identify anatomical, metabolic, ionic, and hemodynamic changes.

#### Oro-nasal airflow via a pressure transducer

A pressure transducer will be used to detect the mean respiratory disturbance index (RDI), before and after 1 and 3 months of intervention.

#### Epworth Sleepiness Scale (ESS)

ESS will be used to analyze the level of daytime sleepiness. Self-assessment will be done by the participants of both the study group before the intervention and after1 month and 3

months of intervention and score will be noted and compared

### Outcome measure

#### Primary outcome

The primary outcome will be the change in the score of AHI, SpO2, REM, EEG, ECG, RDI, and ESS from baseline to the end of 1 month of intervention by MAD and CMOA.

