**Methods:**

A prospective interventional study with a randomized controlled trial will be carried out involving 40 participants (sample size), with an apnea-hypopnea index (AHI) > 15–30, recorded on polysomnography (PSG). Study participants will be randomly divided into the following treatment groups: control group or group subjected to mandibular advancement device (MAD, *n*=20) and second group subjected to customized maxillary oral appliance (CMOA, *n*=20). Baseline assessment of apnea/hypopnea index (AHI), oxygen saturation in blood, percentage of rapid eye movement, electroencephalogram, electrocardiogram, oro-nasal airflow via a pressure transducer, and Epworth Sleepiness Scale will be done. Then both study group participants will receive their respective appliances. And after one month and three months of delivery of the appliance, all the parameters, i.e., AHI, oxygen saturation in blood, percentage of rapid eye movement, electroencephalogram, electrocardiogram, oro-nasal airflow via a pressure transducer, and Epworth Sleepiness Scale will be re-evaluated and compared with the baseline measurements. Descriptive and analytical statistics will be done. SPSS (Statistical Package for Social Sciences) Version 20.1 will be used as statistical software. The statistical significance between the two groups after one month and three months will be evaluated at *p*< 0.05.

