### Statistical analysis

The baseline measures before intervention will be compared with the measures obtained after 1 month and 3 months of intervention. Descriptive and analytical statistics will be done. The data will be presented in mean and standard deviations. The normality of data will be tested by the Shapiro-Wilk test. If the data follows normal distribution parametric tests (Independent sample *t*-test and paired *t*-test) will be used and if the data does not follow normal distribution non-parametric tests (Mann-Whitney *U* test and Wilcoxon signed rank test) will be used. The statistical significance will be set at *p*< 0.05. SPSS (Statistical Package for Social Sciences) Version 20.1 (IBM Corporation, Chicago, USA) will be used as statistical software. The inverse probability censoring weighting (IPCW) approach will be done to estimate a treatment effect in the hypothetical scenario.

We expect to confirm the efficacy of the CMOA in managing moderate OSA against MAD by monitoring AHI, SpO2, REM, EEG, ECG, oro-nasal airflow via a pressure transducer, and ESS before and after 1 month and 3 months.

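### Seven measures are named primary at 1 month, with significance at p<0.05 and no lead variable, adjustment or success rule, so the main claim has no defined test and no controlled error rate

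*Protocol article*

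**What the plan says.** All references are to the protocol article.

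- **Primary outcome:** this section reads "The primary outcome will be the change in the score of AHI, SpO2, REM, EEG, ECG, RDI, and ESS". The comparison is of month 1 with baseline. The list is neither a composite nor ranked.
- **Secondary outcome:** the same seven measures again, this time involving 3 months.
- **Oxygen saturation in the blood (SpO2):** "Mean oxygen saturation, oxygen desaturation index (ODI), and proportion of time with SpO2 < 90%, will be evaluated". One of the seven items is thus three variables.
- **Electroencephalogram (EEG):** the pattern is read "to record Cortical arousals", with no single score defined.
- **Electrocardiogram (ECG):** "The ECG will be evaluated to identify anatomical, metabolic, ionic, and hemodynamic changes". No numeric endpoint is given.
- **Statistical analysis:** "parametric tests (Independent sample *t*-test and paired *t*-test) will be used" if the data are normal, with Mann-Whitney and Wilcoxon tests otherwise. The threshold is stated once for all of them: "The statistical significance will be set at *p*< 0.05".
- **Abstract, Methods:** "The statistical significance between the two groups after one month and three months will be evaluated at" the same 0.05 level.
- **Abstract, Discussion:** if the hypothesis is confirmed, the new appliance is to be cited as a gold standard for moderate OSA. The article does not say which result would confirm it.

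**The concern.** A primary outcome should tell the reader which comparison decides the trial and how often that comparison would mislead by chance. Here seven measures share the primary label, the planned tests take one variable at a time, and one unadjusted threshold covers them all. If AHI shows no difference but ESS or time below 90% saturation does, the plan does not say whether CMOA has been shown to be better. The authors would have to decide that after seeing the results, and the stated 0.05 would not be the error rate of their conclusion. A strong conclusion is meant to rest on it, namely that a new device becomes the reference treatment for moderate OSA.

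**Working it through.** **The plan's own figure.** The Study design section gives a minimum of 16 per group at 80% power, with 20 per group recruited. It states no outcome, effect size, SD or sidedness, so 16 cannot be reproduced or tied to any of the seven measures. Solving backwards with the normal approximation (two-sided 0.05, 80% power) gives a standardised difference d = (1.960 + 0.842) × √(2/16) = 0.99. This figure is an assumption used only under the fix.

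**Counting the primary variables.** The Primary outcome section names 7. The SpO2 section replaces one of these with 3, so 7 − 1 + 3 = 9. This counts EEG and ECG as one variable each. Neither has a defined score, so the count could differ.

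**Chance of at least one false positive at month 1.** Each variable is taken to be tested between arms at two-sided 0.05. The article does not state sidedness. Under independence:

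- 7 tests: 1 − 0.95^7 = 30.2%
- 9 tests: 1 − 0.95^9 = 37.0%

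Counting only false positives in favour of CMOA (0.025 per test), against a nominal 2.5%:

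- 7 tests: 1 − 0.975^7 = 16.2%
- 9 tests: 1 − 0.975^9 = 20.4%

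**Allowing for correlation.** The outcomes overlap, but the article gives no correlations, so a common value r is assumed, with each measure signed so that positive favours CMOA. For jointly normal test statistics, with c = 1.96, the error rate is 1 − ∫ P(u)^k φ(u) du. Here P(u) = Φ((c − √r·u)/√(1−r)) − Φ((−c − √r·u)/√(1−r)). The second term is omitted for the favourable direction.

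| Assumed r | 7, either direction | 9, either direction | 7, favours CMOA | 9, favours CMOA |
|---|---|---|---|---|
| 0 | 30.2% | 37.0% | 16.2% | 20.4% |
| 0.3 | 27.2% | 32.6% | 13.7% | 16.5% |
| 0.5 | 23.0% | 26.9% | 11.5% | 13.5% |
| 0.7 | 17.8% | 20.2% | 8.9% | 10.1% |
| 0.9 | 11.4% | 12.4% | 5.7% | 6.2% |
| Nominal | 5% | 5% | 2.5% | 2.5% |

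Every entry is more than twice its nominal level. The within-arm paired tests and all 3-month tests are left out of this count.

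**The case against.** **Multiplicity rules belong in the analysis plan, which is not shown.** Such a plan could add an adjustment. It could not undo the fact that the article itself fixes seven measures as primary without ranking them. The point rests on what is stated, not on a missing detail.

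**The measures are strongly related, so independence overstates the inflation.** This stands. The Discussion defines RDI almost as AHI, cites a correlation between ODI and AHI, and expects the parameters to move in proportion to one another. The REM measure is AHI within REM sleep. The independent figures are therefore an upper end, but the excess remains even at r = 0.9.

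**The Discussion wants several tools to agree, not one to win.** It does argue against relying on a single tool and presents the other measures as confirming the results. If all measures had to succeed, type I error would not be inflated and the difficulty would be power. No such rule is written, however. A reader might equally infer that the plan lets any one significant measure count as success, and the article does not say that either. What it supports is that no decision rule is stated.

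**Stronger readings that fail.** A reader might count nine variables at two visits and quote 1 − 0.95^18 = 60% as the error rate of the primary claim. The abstract does apply 0.05 at both visits, but the Secondary outcome section makes the 3-month changes secondary, so that figure mixes primary and secondary tests. A reader might also take the gold-standard statement as a foregone conclusion. It is conditional on the hypothesis being confirmed.

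**Conclusion.** The concern holds. As written, the primary claim has no defined test and no controlled error rate. The chance of at least one false positive at month 1 is 11–27% for seven outcomes or 12–33% for nine variables at assumed common correlations of 0.9 to 0.3, with 30% and 37% as the independent upper ends, against 5%. For the error that matters most here, a chance result in favour of CMOA, the figures are 6–14% or 6–17%, with 16% and 20% as upper ends, against 2.5%.

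The sizes rest on four assumptions: each variable is tested between arms at two-sided 0.05, EEG and ECG give one testable variable each, a single correlation is common to all pairs, and one significant result could be presented as success because nothing excludes it. The conclusion that the win is undefined needs none of them. This must be fixed because it concerns the primary outcome itself.

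**What to change.** Name the between-arm difference in AHI change from baseline to 1 month as the single primary outcome, tested two-sided at 0.05. This keeps the protocol's own primary visit, uses the measure that defines eligibility, and follows the Discussion's description of AHI by PSG as the standard for diagnosing and grading OSA. Make the other six measures, and all 3-month measures, secondary. Report them as estimates with 95% confidence intervals, or test them in a fixed order or with Holm if p-value claims are wanted. They then still serve as the supporting evidence that the Discussion asks for.

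A single primary outcome keeps alpha at 0.05 and leaves the stated 16 per group untouched by multiplicity. Keeping all the measures primary with a Bonferroni split (0.05/7 = 0.0071 or 0.05/9 = 0.0056) would cost more. At the back-solved d = 0.99, power for any one outcome with 20 per group would be about 67% or 64% by the normal approximation.

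The cost is more than a change of wording. The Protocol amendments section requires a signed written amendment and approval by the ethics committee and competent authorities, with written re-consent for relevant changes. The Trial status section reports 20 participants included by 2 November 2020 and recruitment expected to be complete by 1 June 2021. The amendment must therefore be dated and made before outcomes are compared by arm. No extra data are needed. The remaining downside is that six measures lose their primary label.

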#### Secondary outcome

The change from baseline in the score of AHI, SpO2, REM, EEG, ECG, RDI, and ESS at the end of 3 monthsThe change in the score of AHI, SpO2, REM, EEG, ECG, RDI, and ESS at the end of 1 month and 3 months of intervention

### Safety evaluation

Adverse events (AEs), including AEs related to PMMA allergy, TMJ pain or muscle pain due to an increase in the vertical dimension of occlusion, gag reflex due to extension of appliances in the soft palate, and others will be recorded. For safety assessment, details of all such adverse events will be recorded by a research assistant in the case report form. Any serious adverse events will be reported within 24 h to the Institutional Ethics Committee.

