However many long-term model analysis studies have reported several side effects of MAD, such as tooth pain, temporomandibular joint disorders, xerostomia or excessive salivation, and gum irritation [15–17]. At the same time, some studies have shown that TMD symptoms in patients using occlusal splint last up to 3–4 months. For most patients, the symptoms disappeared after 5 years [18].

Given the high prevalence of OSA among the population and the side effects of existing appliances, new effective treatment options would be welcomed. The present study focuses on a novel OA named customized maxillary oral appliance (CMOA), to provide a new therapeutic option for patients with moderate OSA. This protocol will help to undertake the study to evaluate the efficacy of this CMOA against MAD for managing mild to moderate OSA.

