## Intervention

### Mandibular advancement device (MAD) Fig. 2

MAD will be fabricated for the Control Group. An impression of upper and lower jaws will be made for all the participants of this group and will be poured to form a cast. A protrusion index will be recorded using a George Gauge by protruding the mandible to 50% of the maximum protrusion. (roughly 6 mm). The appliance will have an upper and lower part of the elastomer and will be interconnected with a screw that will be tightened by advancing the mandible by 6 mm from its centric position. Symptoms related to temporo-mandibular disorder (TMD) will be evaluated. All the patients will be advised to wear the appliance daily while sleeping at least for 6 h.

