#### Fabrication

Impressions of the upper and lower arch of the second group to be treated with the CMOA will be recorded. The cast obtained from the impression will be scanned for CAD designing with the help of CAD software. The design will be 3D printed in polymethylmethacrylate (PMMA ) material and will be delivered to the patient. All the patients will be advised to wear the appliance daily while sleeping at least for 6 h.

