## Discussion

CPAP and OA are the standard treatment modalities for OSA. Zhang M et al. and Schwartz M et al. performed a meta-analysis on the effectiveness of oral appliances versus continuous positive airway pressure in treating OSA. They concluded that comparatively, CPAP is more efficient in reducing AHI, but it has significantly lower compliance resulting in no differences with MAD in quality of life, cognitive, or functional outcomes [19, 20].

Several designs of OA for managing moderate OSA have been documented, among which MAD is the most effective and recommended one [21, 22]. This study is an attempt to benchmark the CMOA as a treatment modality in managing cases with moderate OSA.

Cardinal features of the CMOA are-
The overextension in the soft palate area for its supportA bulge on its palatal surface to prevent the backfall of the tongueA hole in the anterior region to promote continuous inflow of airThe hollowness of the plate to direct airflow towards the pharynxUse of CAD-CAM for precision

The design of this CMOA, recommends an increase in vertical dimension by 2 mm, which facilitates the forward and downward movement of the mandible that contributes to increasing the airflow by maintaining the patency of the airway. Patients of the age group 40-50 years often show the loss of vertical dimension of occlusion, this appliance will also help to regain the vertical dimension and re-establish the original centric relation in such patients [23]. Thus will simultaneously treat the symptoms of Temporomandibular disorders (TMD) if present due to loss of vertical dimension. This appliance will not lead to any changes in dentition as seen among patients treated with MAD.

Evaluating AHI by PSG is considered to be a gold standard for diagnosing and grading OSA. Events of Obstructive apnea (10 s cessation of airflow) and hypopnea (50% or less than 50% reduction in airflow) will be recorded as per the manual of the American Academy of sleep medicine [24]. Isacsson G et al in 2016 compare the effect of monobloc and bibloc appliances on AHI. AHI showed mean declined values of 12.7 and 13.8 for monobloc and bibloc, respectively [25].

However, Otero et al. stated that alone AHI is not sufficient to grade the severity of OSA [26]. And hence along with AHI, SPO2, REM, EEG, ECG, and oro-nasal airflow, ESS will also be evaluated in the present study to record the severity of OSA before and after one and three months of intervention by MAD and CMOA.

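### Harm ascertainment is written unevenly by arm: TMD evaluation is stated only for MAD and the named adverse events follow CMOA features, which risks differential ascertainment

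*Protocol article*

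**What the plan says.** Four places in the protocol article bear on how harms are found.

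- **Intervention, MAD.** After the advancement screw is described, the text adds: "Symptoms related to temporo-mandibular disorder (TMD) will be evaluated". It gives no instrument or time point. The CMOA design and fabrication text has no matching sentence.
- **Safety evaluation.** Adverse events are to be recorded, "including AEs related to PMMA allergy, TMJ pain or muscle pain due to an increase in the vertical dimension of occlusion", and "gag reflex due to extension of appliances in the soft palate, and others will be recorded". The section is not limited to one arm. It adds that "details of all such adverse events will be recorded by a research assistant in the case report form".
- **Background.** The reported side effects of MAD are "tooth pain, temporomandibular joint disorders, xerostomia or excessive salivation, and gum irritation". The next paragraph gives the side effects of existing appliances, together with the high prevalence of OSA, as the reason for seeking a new option.
- **Discussion.** A comparative claim is made for the CMOA: "This appliance will not lead to any changes in dentition as seen among patients treated with MAD". The Discussion also expects the CMOA to relieve TMD symptoms that come from lost vertical dimension.

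**The concern.** The article looks for one harm explicitly in the MAD arm only. Its named examples of other harms fit the CMOA, and it does not name most of the harms that it attributes to MAD. A study team that followed this text literally could examine jaw symptoms more closely on MAD, ask more readily about CMOA-type complaints, and hear of tooth pain, dry mouth or gum irritation only when a participant raised them.

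A difference in harm counts between the arms would then partly reflect how the harms were sought. The two unevennesses can push in opposite directions. The TMD sentence would tend to raise counts on MAD. The choice of named events would tend to raise counts on CMOA and to lower oral and dental counts on MAD. The reader of the results could not separate these effects from a real difference between the devices.

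At stake is whether the trial can support the claim that the new appliance spares patients the side effects of MAD. TMJ disorders are an exclusion criterion in both arms, so new TMD symptoms would make a clean comparison if they were measured equally.

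**Working it through.** No arithmetic beyond counting applies, because the article states no harm rates and no probability that a harm is captured. The check sets the sections side by side.

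**Step 1: is the TMD evaluation shared?** It appears once, under MAD. The omission under CMOA cannot be put down to a habit of stating common instructions only once: the wear-time advice ("All the patients will be advised to wear the appliance daily while sleeping at least for 6 h") is written out in both device sections. Shared steps are repeated, and this one is not.

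**Step 2: which device do the named events describe?**

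| Named event (Safety evaluation) | CMOA text | MAD text |
|---|---|---|
| PMMA allergy | printed in PMMA | upper and lower parts of elastomer |
| TMJ or muscle pain from raised vertical dimension | built at an increased vertical dimension | advancement of the mandible is described; no such increase is stated |
| Gag reflex from soft-palate extension | base plate extended 1 mm in that region | no such extension is described |

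Count: 3 of 3 named events carry a stated feature of the CMOA.

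**Step 3: which MAD side effects are named?**

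| MAD side-effect group (Background) | Named in Safety evaluation? |
|---|---|
| Tooth pain | no |
| TMJ disorders | yes, as TMJ or muscle pain, tied to vertical dimension |
| Xerostomia or excessive salivation | no |
| Gum irritation | no |

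Count: 1 of 4 groups named, so 4 − 1 = 3 unnamed. Change in dentition, on which the Discussion makes its comparative claim, is not named either.

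**Step 4: does the wording of the items matter?** Two of the three named events include a cause: "TMJ pain or muscle pain due to an increase in the vertical dimension of occlusion" and the soft-palate extension in the gag item. TMJ pain that a MAD wearer attributes to the forward position of the jaw does not literally match the first of these. Whoever records it must judge the cause before choosing the item.

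**Step 5: what limits the inference?** The list opens with the word including and ends with a catch-all, and the section covers both arms. The unnamed MAD harms can therefore be recorded, and so can TMJ or muscle pain on CMOA. The text does not say which events are asked about and which are left to spontaneous report.

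**The case against.** The case on the other side has several parts.

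- **The list is open and common to both arms.** This stands. Nothing in the Safety evaluation section prevents tooth pain on MAD or TMJ pain on CMOA from being recorded.
- **The TMJ item may fit both devices.** The Background says that MAD holds the mandible forward and downward, and a downward position could also open the bite. This is a fair reading and weakens the claim that the item belongs to the CMOA alone. It does not reach the PMMA and soft-palate items.
- **The TMD sentence may be a fitting check, not outcome assessment.** It sits between the screw setting and the wear advice and has no time point. This is possible. If it is the intent, the text should say so, because a literal reading still gives TMD evaluation to one arm.
- **A fuller case report form may list the same harms in both arms.** It may. The point, however, is not that detail is absent. What the article does state is uneven, and a form built from it would inherit that.
- **No safety comparison is specified, and harms are not among the primary or secondary outcomes.** This is correct and limits the weight of the point. The Background and Discussion nevertheless argue from comparative harm.

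A reader might go further and infer that the whole MAD side-effect list is ignored, or that TMD on CMOA is left to spontaneous report, and might then put a figure on a spurious advantage for CMOA. The documents do not support this. TMJ pain is on both lists, the Safety evaluation section names TMJ or muscle pain for recording in both arms, and any capture rates would be invented.

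**Conclusion.** The point holds as a risk of differential ascertainment, not as a demonstrated bias. In countable terms, the TMD evaluation is stated in one arm of two, 3 of 3 named adverse events are worded around CMOA features, and 3 of 4 MAD side-effect groups are unnamed. The net direction is unclear, and no size in percentage points can be given.

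The conclusion assumes that conduct follows the article's text and that the case report form, which is not shown, does not already even out the two arms. The efficacy comparison is not affected. The change is worth making because it is cheap and because the article's own argument for the CMOA relies in part on fewer side effects than with MAD.

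**What to change.** State that the TMD evaluation applies to both arms, with the same method and at the same visits. Replace the device-specific examples by one harm checklist, identical in both arms, completed at baseline, 1 month and 3 months by the research assistant already named in the Safety evaluation section. It should cover:

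- TMJ or muscle pain, and the TMD evaluation
- tooth pain
- dry mouth or excess saliva
- gum irritation
- gag reflex
- material reaction, for whichever material is used
- any other event

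Take the cause out of the item wording, so that an event is recorded first and attributed separately. Report the number of participants with each item by arm.

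The cost is about one extra form page at visits that already take place. Counts will be higher in both arms. Participants already enrolled may lack baseline answers: the Trial status section reports 20 included by 2 November 2020, which is half of the planned 40. For anyone assessed before the change, the report should say how harms were sought in each arm.
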